### Ethics Approval and Informed Consent

The Heidelberg Ethics Committee approved this study on June 26, 2017 (S-216/2017). Inclusion of a patient into this trial requires meeting the above-mentioned inclusion and exclusion criteria as well as the patient’s written informed consent. Continuous information will be supplied to the committee about all changes to the study that may influence patient safety, as well as about the conclusion or discontinuation of the study. Participation in the clinical trial is voluntary for subjects. Before inclusion in the study, a potential subject will be thoroughly and in detail informed about the nature, aims, risks and benefits of the study before informed consent can be given. Detailed information will be provided in a fashion and language understood by the patient.

An informational handout as well as an informed consent form—both documents conforming to the standards of the International Conference on Harmonization-Good Clinical Practice—will be provided to the patient before inclusion. Informed consent must be given only after an appropriate amount of time for consideration and then must be in writing and complemented with information about date and time of signature in the patient’s own handwriting. Informed consent must be countersigned by the treating physician. If a patient is incapable of signing the informed consent form, oral informed consent must be confirmed by the signature of a witness.

Clinical subjects are free to refuse to participate in the study or to withdraw from it at any time for any reason without incurring any penalty or withholding of treatment on the part of the investigator. This study includes no additional invasive or otherwise harmful or burdening procedures.

**Table 1 table1:** Intervention and assessment schedule for the OPTIMISE-1 trial.

Steps		Enrolment	Allocation	Start of RT^a^	End of RT	First follow-up
**Enrolment**						
	Eligibility screen	✓				
	Informed consent	✓				
	Allocation		✓			
**Interventions**						
	RT			✓	✓	
	Patient support with help of a mobile app			✓	✓	
**Assessments**						
	EORTC QLQ^b^			✓	✓	✓
	# of app-based questions answered				✓	
	Patient satisfaction (PSQ-18^c^)				✓	
	Frequency and length of consultations				✓	✓

^a^RT: radiotherapy.

^b^EORTC QLQ: European Organisation for Research and Treatment of Cancer quality of life questionnaires.

^c^PSQ-18: Patient Satisfaction Questionnaire Short Form.

## Results

The results of this trial will be published in a peer-reviewed journal within 24 months of trial initiation, independently of the outcome of the trial. Publication will be prepared under the lead of the principal investigator of the study. The first and last authorship will be assigned by the principal investigator.

## Discussion

### Study Rationale

As consumer electronics become increasingly employed in the medical sector, their use for the support of oncologic patients opens up a range of possibilities from the gathering of information on patient health and symptoms to patient notification about appointments or test results. The present single-center prospective pilot trial conducted at the Department of Radiation Oncology of Heidelberg University Hospital explores the possibility of employing a mobile app for the systematic support of radiooncological patients throughout the course of their radiotherapy by monitoring symptoms and patient performance, and facilitating the exchange of relevant information between patient and physician. We aim to assess the feasibility and patient acceptance of incorporating such a mobile app into active patient care. Furthermore, we aim to estimate the economic and financial aspects of this novel approach to therapy support.

### Limitations and Future Perspectives

In the current study, the survey app is not deployed using the patient’s own mobile device but is installed on a tablet computer belonging to the investigator and integrated into the institution’s information technology infrastructure according to data protection regulations. For future trials, it is planned (after establishing feasibility and usefulness) to expand the scope of the app so that patients can use their own devices for survey completion outside the clinic.

On the other side, the aforementioned approach may contribute to addressing a possible selection bias. By presenting the application to patients on an institution-owned tablet device, we do not exclude patients who do not themselves own a mobile device, thus testing the application on patients regardless of their technical abilities and/or affinity.

The definition of feasibility in this trial is largely derived from intrainstitutional clinical experience and logistical considerations. There is, however, to date no systematic data from which a more general definition of feasibility can be derived in this context. A systematic survey conducted at our institution on oncologic patients’ use of and affinity towards mobile devices is in accordance with previously published data [13] in suggesting that roughly three quarters of patients would be inclined to use a mobile app in the context of radiotherapy. This further suggests that expecting a patient compliance of 80% to demonstrate feasibility is realistic.

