### Statistical Analysis

The calculation of the sample size was done with respect to the primary endpoint and the primary analysis. Using the exact binomial test, we aim to show that the primary endpoint is reached at values of ≥80% of all study subjects answering ≥80% of the app-based questions during their radiotherapy as outpatients. With a sample size of 50 patients in this pilot study and an assumed percentage of 92% for the primary endpoint, a power of 1-β=80% is reached with a one-sided significance level of α=5%. Considerations regarding sample size and power were done using the *PROC POWER* procedure in SAS (version 9.4). The primary endpoint will be evaluated using the exact binomial test, which is the primary analysis. The one-sided significance level for this feasibility study is set to 5%.

Methods of descriptive data analysis will be used to describe patient characteristics and secondary outcomes, including calculation of appropriate summary measures of the empirical distribution, such as mean and standard deviation, median and interquartile range for continous variables, as well as absolute and relative numbers for categorical variables. Additionally, according to tumor type, subgroup analyses will be performed as a sensitivity analysis. Additionally, multivariable regression models will be used to analyze the relationship between patient characteristics and the primary endpoint. However, we will consider the primary variable on the original scale without any cut-off value (ie, the relative number of app-based answered questions) as the outcome variable and, thus, linear regression models will be applied. Age, gender and the need of toxicity-caused hospitalization will be included as predictors. The same model will be applied for the secondary endpoints. In addition, correlations will be considered. Graphical methods will be applied to visualize the results.

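### The Abstract and Discussion treat 80% of patients complying as enough to show feasibility, but 80% is the null value of the primary test, which needs at least 45 of 50 (90%)

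*Protocol article*

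**What the plan says.** **Statistical Analysis (Methods).** The aim is worded as "we aim to show that the primary endpoint is reached at values of ≥80% of all study subjects answering ≥80% of the app-based questions". The test is named without ambiguity: "The primary endpoint will be evaluated using the exact binomial test, which is the primary analysis". The planning assumption is "With a sample size of 50 patients in this pilot study and an assumed percentage of 92% for the primary endpoint", for which the article states 80% power at a one-sided 5% level. The section does not label 80% as the null value and gives no minimum number of successes.

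**Limitations and Future Perspectives (Discussion).** In a paragraph on how feasibility was defined, the article reports that an institutional survey, in line with published data, suggests that "roughly three quarters of patients would be inclined to use a mobile app in the context of radiotherapy". It then concludes: "This further suggests that expecting a patient compliance of 80% to demonstrate feasibility is realistic". The 92% is not mentioned there.

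**Abstract (Methods).** Feasibility counts as reached when 80% of patients have answered 80% of their scheduled questions. No test is mentioned.

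**The concern.** The article gives two different answers to the question of how many of the 50 patients must succeed. The Abstract and Discussion imply 80%, which is 40 of 50. The Statistical Analysis section makes an exact test the primary analysis, and a test against 80% can succeed only if the observed proportion is well above 80%.

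With 40 to 44 successes, one reader could declare feasibility from the Abstract while another reports a failed primary analysis. The choice between the two would be made after the data are seen. The conclusions say that the trial prepares larger evaluations, so the verdict matters.

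The survey adds a second difficulty. It is offered as support for the 80%, but it is below 80% and measures something other than the endpoint.

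**Working it through.** **Inputs.** n = 50, assumed true proportion 0.92, exact binomial test, one-sided α = 0.05, stated power 80% (all from Statistical Analysis). The null value p0 = 0.80 is inferred from the aim stated there. The article gives no dropout allowance, so none is used.

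**Step 1: critical value.** Find the smallest r with P(X ≥ r | n = 50, p = 0.80) ≤ 0.05.

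- P(X ≥ 44 | 0.80) = 0.1034, too large.
- P(X ≥ 45 | 0.80) = 0.0480, acceptable.

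So r = 45, or 45/50 = 90% observed, with an actual type I error of 4.8%.

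**Step 2: reproduce the stated power.** P(X ≥ 45 | 0.92) = 0.7919, or 79.2%, which agrees with the stated 80%. At one-sided 2.5% the critical value would be 46 and the power 62.9%, which does not agree. A null of 80% at one-sided 5% is therefore the design that fits the article's own figure.

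**Step 3: compare the two success rules.** The last column is the second minus the third. It is the chance that the result falls at 40 to 44, where the two rules disagree.

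| True proportion | P(X ≥ 40): observed 80% or more | P(X ≥ 45): primary test | Difference |
|---|---|---|---|
| 0.80 | 0.5836 | 0.0480 | 0.5356 |
| 0.85 | 0.8801 | 0.2194 | 0.6607 |
| 0.90 | 0.9906 | 0.6161 | 0.3745 |
| 0.92 | 0.9983 | 0.7919 | 0.2064 |

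The entry 0.0480 at a true 0.80 is the type I error. The test-column entries from 0.85 upwards are power.

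**Step 4: what a failed test would say about 92%.** These are exact (Clopper-Pearson) two-sided 95% intervals. The lower limit solves P(X ≥ x | p) = 0.025 and the upper limit solves P(X ≤ x | p) = 0.025.

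| Successes | Observed | Exact 95% interval | Contains 92%? |
|---|---|---|---|
| 40 | 80% | 66.3% to 90.0% | no |
| 41 | 82% | 68.6% to 91.4% | no |
| 42 | 84% | 70.9% to 92.8% | yes |
| 43 | 86% | 73.3% to 94.2% | yes |
| 44 | 88% | 75.7% to 95.5% | yes |

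All five results fail the test, but they do not all carry the same message.

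**The case against.** **The Discussion sentence may only set the bar.** Its paragraph is about the definition of feasibility, so the sentence can be read as requiring more than 80%, which is how the test is built. It could also refer to the share of questions each patient answers, which the endpoint section justifies by logistical irregularities. Both readings are possible. Neither rescues the inference: a survey share of about 75% does not make an 80% bar realistic, and willingness to use an app says nothing about the share of questions answered. The Abstract's wording also remains, and it conflicts with the test on any reading.

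**A reader might infer that the trial has 1% to 5% power instead of 80%.** The document does not support that. The 80% is expressly conditional on 92% and is right for that rate. The 4.8% at a true 80% is the type I error at the null, and any rate below 80% lies inside the null. Every valid 5% test behaves this way, so these figures show no shortfall in the design.

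**A reader might take 75% as the expected endpoint rate.** That does not follow either. The survey concerns inclination to use an app among patients generally. The endpoint is adherence among enrolled patients, with an assumed consent ratio of 5% to 10%, using an institution-owned tablet in the clinic.

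**No source is given for 92%.** In a condensed article this is not a finding, since the full protocol may give one. Only the mismatch between the printed passages is raised here.

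**Conclusion.** The article contradicts itself on the decision threshold. The Abstract and Discussion present 80% of patients as sufficient, while the primary analysis needs 45 of 50. The conflict changes the conclusion for 40 to 44 successes. Such a result has a 21% chance if the true rate is the planned 92%, 37% at 90% and 66% at 85%.

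The sample size and power calculation stand: 79.2% at 92%. That power is sensitive to the planning rate, falling to 62% at 90% and 22% at 85%, and the survey cannot support the planning rate or the 80%.

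This rests on 80% being the null value, which the article does not state in words but which its own power figure confirms, and on all 50 patients being evaluable. The remedy is a correction of wording; endpoint, test, level and N stay as they are.

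**What to change.** Keep N = 50 and the primary test.

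1. **Statistical Analysis:** state that the null hypothesis is a proportion of 80% or less, that with 50 evaluable patients feasibility is declared only with at least 45 successes, and that the 79% power is conditional on a true rate of 92% (62% at 90%, 22% at 85%).
2. **Limitations and Future Perspectives:** remove the inference that the survey makes 80% realistic. Say that 92% among consenting patients is the planning assumption and that the survey concerns general willingness. Align the **Abstract** with the 45/50 rule.
3. **Interpretation:** report the exact confidence interval with any result and read a non-significant result from it. Do not label everything from 80% to 88% inconclusive: 40/50 and 41/50 exclude the planned 92%, while 42/50 to 44/50 do not. State that the test decides. At 45/50 its one-sided p-value of 0.048 lies between 0.025 and 0.05, so a two-sided 95% interval still includes 80%, whereas a two-sided 90% interval, which matches the one-sided 5% level, does not.

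The cost is a few sentences, with no added patients or procedures. The downside is presentational: the required success rate and the power look less favourable than the current text suggests.

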### Conclusions

The findings of this study will play an important role in clinically validating the mobile app we have developed for the collection of patient-reported outcome measures from patients undergoing radiotherapy. By proving the usefulness and feasibility of an app-based approach to radio-oncologic patient supportive care, the present exploratory study prepares the ground for the larger-scale evaluations we are planning to perform on this promising subject.

## Appendix

Multimedia Appendix 1 SPIRIT checklist of different protocol items related to this trial.

## Abbreviations

EORTC: European Organisation for Research and Treatment of Cancer
mHealth: mobile health
OPTIMISE-1: Oncologic Therapy Support Via Means of a Dedicated Mobile App – A Prospective Feasibility Evaluation
PSQ-18: Patient Satisfaction Questionnaire Short Form
QLQ: quality of life questionnaire
QoL: quality of life
ROKIS: Radiation Oncology Clinic Information System
SOP: standard operating procedures
SPIRIT: Standard Protocol Items: Recommendations for Interventional Trials
